## Abstract

**Background:**

Therapy guidelines recommend speech and language therapy (SLT) as the “gold standard” for aphasia treatment. Treatment intensity (i.e., ≥5 hours of SLT per week) is a key predictor of SLT outcome. The scientific evidence to support the efficacy of SLT is unsatisfactory to date given the lack of randomized controlled trials (RCT), particularly with respect to chronic aphasia (lasting for >6 months after initial stroke). This randomized waiting list-controlled multi-centre trial examines whether intensive integrative language therapy provided in routine in- and outpatient clinical settings is effective in improving everyday communication in chronic post-stroke aphasia.

**Methods/Design:**

Participants are men and women aged 18 to 70 years, at least 6 months post an ischemic or haemorrhagic stroke resulting in persisting language impairment (i.e., chronic aphasia); 220 patients will be screened for participation, with the goal of including at least 126 patients during the 26-month recruitment period. Basic language production and comprehension abilities need to be preserved (as assessed by the Aachen Aphasia Test).

Therapy consists of language-systematic and communicative-pragmatic exercises for at least 2 hours/day and at least 10 hours/week, plus at least 1 hour self-administered training per day, for at least three weeks. Contents of therapy are adapted to patients’ individual impairment profiles.

Prior to and immediately following the therapy/waiting period, patients’ individual language abilities are assessed via primary and secondary outcome measures. The primary (blinded) outcome measure is the A-scale (informational content, or 'understandability’, of the message) of the Amsterdam-Nijmegen Everyday Language Test (ANELT), a standardized measure of functional communication ability. Secondary (unblinded) outcome measures are language-systematic and communicative-pragmatic language screenings and questionnaires assessing life quality as viewed by the patient as well as a relative.

The primary analysis tests for differences between the therapy group and an untreated (waiting list) control group with respect to pre- versus post 3-week-therapy (or waiting period, respectively) scores on the ANELT A-scale. Statistical between-group comparisons of primary and secondary outcome measures will be conducted in intention-to-treat analyses.

Long-term stability of treatment effects will be assessed six months post intensive SLT (primary and secondary endpoints).

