### Objective

This prospective randomized controlled endpoint-blinded trial aims to examine whether, in chronic aphasia, the integrative approach to intensive language and communication therapy translates into functional improvements of everyday communication as well as improved health-related quality of life.

The principal research question is two-fold: (i) how effective is intensive integrative (i.e. combined language-systematic and communicative-pragmatic) language therapy, as currently administered in German in- and outpatient aphasia rehabilitation facilities, in improving everyday communication in post-acute/chronic post-stroke aphasia; and (ii) to what degree are these improvements maintained over a period of 6 months?

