### Study design

The study design is depicted in Figure 1. The inclusion of a waiting list control group, intended to control unspecific effects of language therapy, circumvents the ethical dilemma of withholding potentially efficacious treatment from patients. After a 3-week waiting period, the control group receives the same treatment as the experimental group.

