#### *Primary analysis*

The primary endpoint will be evaluated at baseline (t1) and immediately after 3 weeks of intensive therapy/waiting period (t2), by a statistical between-group comparison of the ANELT A-scale (ANCOVA) in an ITT design and with methods of multiple imputation taken into account. We expect that monotone missing data patterns will be observed (as described in [33]) and techniques appropriate for this situation will be applied. As a sensitivity analysis, the last-observation-carried-forward method will be applied.

Based on prior studies, we expect a therapy-induced improvement on the ANELT A-scale of M = 10 points (SD = 14) from baseline to immediately after 3 weeks of intensive therapy in the intensively treated group. For the waiting list group, we expect a change of M = 1 point (SD = 10) from baseline (t1) to the end of the 3-week waiting period (t2).

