#### *Secondary analyses*

Performance on the ANELT A-scale will also be evaluated at baseline (t1) and immediately after 3 weeks of intensive therapy/waiting period (t2), by a statistical between-group comparison of the ANELT A-scale (ANCOVA) in a treated-per-protocol design. In patients who are granted an extension beyond 5 weeks of intensive language therapy by their respective sickness fund, performance on the ANELT A-scale from pre to post therapy will again be evaluated immediately after the total intensive therapy period (i.e., 5–7 weeks after the baseline assessment = t2b), by a statistical between-group comparison of the ANELT A-scale (ANCOVA) in an ITT design where the last observation will be carried forward. This design feature is required due to the current heterogeneous therapy funding practices by the sickness funds. Initial funding is generally granted for 3 weeks, and for some patients (about 20%) extended for up to 7 weeks. The decision about the extension is made *after* rehabilitation therapy has started. Therefore, total duration of therapy cannot be planned *a priori*. Secondary endpoints (language-systematic and communicative-pragmatic screening measures; German version of the SAQOL-39, German Version of the CETI, ANELT B-scale as well as syntactic and non-verbal communication ratings) will be analysed in analogy to the primary analysis at baseline (t1) and immediately after 3 weeks of intensive therapy/waiting period (t2), by a statistical between-group comparison (ANCOVA) in an ITT design. Where applicable, the secondary endpoints will again be evaluated after a variable therapy extension for up to 7 weeks total therapy (t2b) in a subgroup of patients (cf. secondary analysis of the ANELT A-scale). Maintenance of therapy gains will be evaluated 6 months after termination of the first 3 weeks of intensive therapy (t4, long-term outcome) by statistical comparisons with t1, respectively. The amount of outpatient therapy provided between t2/t2b and t4 will be statistically controlled by covariate analyses.

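### The six-month comparison (t4 versus t1 within each group) has no untreated comparator, so it cannot show long-term stability of treatment effects

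*Protocol article*

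**What the plan says.** All references are to the protocol article.

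- **Abstract, Methods/Design:** "Long-term stability of treatment effects will be assessed six months post intensive SLT (primary and secondary endpoints".
- **Objective:** the second half of the principal research question asks "to what degree are these improvements maintained over a period of 6 months".
- **Study design:** "After a 3-week waiting period, the control group receives the same treatment as the experimental group".
- **Secondary analyses:** "Maintenance of therapy gains will be evaluated 6 months after termination of the first 3 weeks of intensive therapy". The comparison named for this purpose is "t4, long-term outcome) by statistical comparisons with t1, respectively". The section Waiting list control group repeats the same t4-versus-t1 comparison for that group. Neither section names a between-group contrast or an untreated reference at t4.
- **Secondary analyses, on care after the therapy block:** "The amount of outpatient therapy provided between t2/t2b and t4 will be statistically controlled by covariate analyses".
- **Primary analysis, on expected changes from t1 to t2:** in the therapy group, "we expect a therapy-induced improvement on the ANELT A-scale of M = 10 points (SD = 14"); in the waiting-list group, "For the waiting list group, we expect a change of M = 1 point (SD = 10) from baseline (t1") to t2. The section Waiting list control group expects 10 points from t1 to t3. No expected value is given for t4.

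**The concern.** Randomisation separates therapy from no therapy only between t1 and t2. From week 3 both groups are treated, so a six-month score cannot be compared with what would have happened without therapy. The abstract nevertheless keeps the language of treatment effects for t4, and maintenance is one half of the principal question.

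Two things are at stake. First, a t4-minus-t1 change could be reported as a lasting treatment effect when the design does not identify one. Second, the question of degree (how much of the gain is kept) is not answered by a test against t1, because such a test only asks whether any difference from baseline remains. In the waiting-list group there is a further fault: t1 lies before the waiting period and is not that group's pre-therapy point, so the comparison credits the waiting-period change to therapy.

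**Working it through.** The article gives no figure for t4, so there is none to reproduce. The check is of structure first, then of size.

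**1. Who is untreated at each test point (Study design; Primary analysis; Waiting list control group)**
- t2: therapy group treated, waiting-list group untreated. A randomised contrast exists.
- t3 (waiting list, after its therapy) and t4 (both groups): no untreated group remains.

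**2. Length of the long-term interval.** Taking six months as 26 weeks after the first three weeks of therapy:
- Therapy group, t1 to t4: 3 + 26 = 29 weeks.
- Waiting-list group, t1 to t4: 3 + 3 + 26 = 32 weeks.
- Waiting-list group, t2 to t4: 3 + 26 = 29 weeks. Only this interval matches the therapy group's t1 to t4.

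**3. What t4 minus t1 contains.** Retained therapy gain + untreated change over 29 or 32 weeks + repeated-testing effect + extended therapy + later care. Extended therapy matters because about 20% of patients are expected to go on for up to 7 weeks in total, while t4 is timed from the end of the first 3. Up to 7 − 3 = 4 further weeks of intensive therapy therefore fall between t2 (or t3) and t4.

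**4. The waiting-period change.** On the plan's figures the waiting list gains 10 points from t1 to t3, of which 1 arises before therapy. The gain over its therapy block is therefore 10 − 1 = 9 points. Measured from t1, a fully kept gain reads as 10; measured from t2, as 9.

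**5. Possible size of untreated change.** The only input is 1 point in 3 weeks.
- One-off (for example practice): 1 point.
- Linear continuation: 29/3 = 9.7 points (therapy group) and 32/3 = 10.7 points (waiting list).

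Both ends are assumptions. The plan's figures lean towards the first. The therapy group's 10 points over 3 weeks, less 1 untreated point, leave 9. Over 6 weeks the waiting list would then show 9 + 1 = 10 if untreated change is one-off, but 9 + 2 = 11 if it accumulates. The plan states 10, although rounding could hide one point.

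**6. Why a test against t1 does not measure maintenance.** Assume 63 patients with t4 data, a paired t-test, and an SD of 14 for the t1-to-t4 change (the SD for t4 is not given; 14 is the therapy group's t1-to-t2 value).
- SE = 14/√63 = 1.76. The smallest significant mean change is 2.00 × 1.76 = 3.5 points.
- With SD 10 it is 2.00 × 1.26 = 2.5 points; with SD 20 it is 2.00 × 2.52 = 5.0 points.

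A t4 gain of a quarter to a half of 10 points would thus already be significant against t1, although half to three quarters of the gain had been lost.

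**7. Whether the observed waiting-list change could be projected to t4.** With SD 10 and n = 63 its SE is 10/√63 = 1.26 points. Scaled linearly to 29 weeks the SE is 1.26 × 29/3 = 12.2, so the 95% interval is about ±1.96 × 12.2 = ±24 points. Such a projection would be uninformative.

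**The case against.** The strongest defence is that the long-term question concerns persistence, which within-patient follow-up can describe. The article openly names t1 as the reference and claims no between-group effect at t4. It places every analysis other than the primary one outside the confirmatory claim. The lack of a later control is a deliberate ethical choice. Parallel ANELT versions are alternated to limit practice effects, the raters do not know the time of assessment, and outpatient therapy after t2 or t2b is adjusted for. An analysis plan that is not shown may contain more.

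Much of this stands: describing persistence is legitimate, and these measures reduce some of the confounding. They do not supply a control. The amount of outpatient therapy is a post-randomisation variable, and adjusting for it leaves untreated change untouched. The non-confirmatory label is tied to the absence of multiplicity adjustment, not to a missing comparator. The comparison and the wording are both stated in the article, so the point does not rest on omitted detail.

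Two stronger readings are tempting and not supported:
- **A reader might infer that untreated change could account for the whole expected gain.** That needs linear continuation for about seven months, which the plan never assumes. Statistical analyses expects no clinically significant change in controls over the wait, and Background contrasts this trial with those begun during spontaneous remission. The 10 points are also stated for t2 and t3, not for t4.
- **A reader might infer that a group that merely drifted upward would be reported as showing a maintained effect.** Pure drift would act on both groups alike and leave no randomised difference at t2 to be maintained. For drift to mimic maintenance, a real t2 effect would have to fade while untreated change of similar size replaced it.

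**Conclusion.** The point holds as a limit on interpretation. With no untreated comparator after week 3, the stated t4-versus-t1 comparison cannot support a claim about stability of treatment effects. On its own it also does not show to what degree the gain was maintained. In the waiting-list group it additionally counts the waiting-period change, 1 point on the plan's own expectation.

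The untreated share of the change over 29 to 32 weeks cannot be determined from the design: 1 point if one-off, about 10 only at an extreme that the plan does not adopt. The structural conclusion depends on neither figure. The statement about significance at 2.5 to 5.0 points assumes 63 patients with t4 data and an SD between 10 and 20. The randomised comparison at t2 is sound in this respect and unaffected.

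**What to change.** 1. In the Abstract, Secondary analyses and Waiting list control group, describe t4 as an uncontrolled within-group outcome and drop the term treatment effects for that time point.
2. Report t4 with confidence intervals against two references: the immediate pre-therapy score (t1 in the therapy group, t2 in the waiting-list group) and the score after the three-week therapy block (t2 or t3 respectively). The first shows the level relative to before therapy. The second addresses how much of the gain was kept.
3. State that untreated change cannot be separated from retained therapy effect at t4.

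No projection of the waiting-list change to six months is advised, because its error would swamp the result.

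The cost is rewording and two reported contrasts on assessments that are already scheduled. The downside is a less favourable six-month claim.

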**Trial registration:**

Registered in ClinicalTrials.gov with the Identifier NCT01540383

## Background

Aging populations and higher survival rates in patients with acute stroke place increasing financial constraints on the health care system, requiring evidence-based interventions in stroke rehabilitation [1-3]. One of the most devastating conditions after stroke is aphasia, a disturbance in language function, which affects about 27% of all stroke patients [4]. About half of the initially affected patients still suffer from aphasia one year after stroke [5-7]. Apart from the emotional burden associated with aphasia [8], language dysfunction in the post-acute or chronic phase after a stroke is a major reason for failure of vocational rehabilitation [9]. Impaired communication ability commonly represents an obstacle to vocational and professional reintegration, thus incurring health care costs and losing potential contributors to the 'social contract’ (i.e., fiscal payments) [10].

Therapy guidelines recommend speech and language therapy (SLT) as the 'gold standard’ for aphasia treatment. Treatment intensity (i.e., ≥5 hours of SLT per week) appears to be a key predictor of SLT outcome [11]. The scientific evidence to support the efficacy of SLT is unsatisfactory to date [12] given the lack of randomized controlled trials (RCTs), particularly with respect to chronic aphasia (lasting for >6 months after the initial stroke). Even though recent evidence-based reviews support the efficacy of intensive aphasia therapy [2,13], the available evidence has not yet led to increased referrals for aphasia patients. This state of affairs may in part be due to a lack of high-quality RCTs with positive outcome as well as to a failure to administer a functional outcome measure. In the age of evidence-based medicine, however, there is a growing demand that SLT should be evidence-based and that outcomes should be operationalized with respect to participative gains [14,15].

Furthermore, motivated by the World Health Organization (WHO) guidelines regarding more patient-centred, outcome-oriented therapy schemes (International Classification of Functioning, Disability and Health [16]), aphasia rehabilitation facilities increasingly apply an integrative naturalistic therapy approach [17-19]. This integrative approach, which may be described as the agreed best practice, consists of both language-systematic and communicative-pragmatic exercises as well as a combination of one-on-one and group therapy settings. In addition, patients are often encouraged to supplement the gains of intensive therapy with self-administered computerized language exercises.

The efficacy of intensive SLT under such 'natural’ therapy conditions, however, has never been investigated in persons with chronic aphasia, although there is mounting evidence consistent with the assumption that SLT is efficacious when treatment intensity is sufficiently high. Specifically, aphasia therapy has been shown to be efficacious when treatment is provided for at least 5 hours per week for a period of several weeks [11]. A 2003 systematic review found that therapy studies which reported positive outcomes had administered an average of 8.8 hours of therapy per week [13]. The authors of this review noted, however, that only few of the studies included were rated to be of good quality; the majority of the studies were either of fair quality or did not fulfil basic quality criteria (such as randomizing participants to conditions). Since then, several empirical studies on SLT in post-acute/chronic aphasia have corroborated the assumption that short periods of intensive SLT (i.e., two weeks duration with several hours of SLT daily) significantly enhance linguistic functions even in the chronic stage after a stroke [20,21], with excellent long-term stability of therapy outcome [21,22]. However, the number of participants in these studies was relatively small; numbers ranged from 12 [21] to 28 [20] individuals with aphasia. Furthermore, apart from questionnaires asking patients and relatives to indicate the estimated level of communicative abilities, primary outcome measures in these studies were operationalized as changes in scores of standardized language test batteries. These types of outcome measures have been increasingly criticized because they do not reflect potential gains in everyday communicative language functions.

In the past two years, several RCTs with large numbers of participants have used primary outcome measures focused on functional communication ability [23-25]. In all of these trials, treatment started within the period of spontaneous remission after the initial stroke. Laska et al. initiated treatment sessions within two days after stroke, and administered 3.75 hours of therapy per week for a period of 21 days [25]. Therapy focused on ameliorating comprehension and naming abilities. After three weeks, no difference was found on the Amsterdam-Nijmegen Everyday Language Test (ANELT) between the treatment group and an untreated control group. Bowen et al. administered on average 18 hours total of agreed best practice of communication therapy over a period of up to four months (i.e., on average less than 2 hours per week) [23]. At six months post onset, no difference in a functional outcome measure was found between the treated group and a control group receiving social contact by contracted “visitors” with a similar frequency.

Compared to the significant improvements found in the studies administering intensive therapy with a frequency of at least 1 hour per day, the latter findings strongly suggest that the negative findings may partly have been due to the fact that therapy was administered with a frequency below the minimum of 5 hours per week recognized as being efficacious [13]. Thus, for patients with stroke-induced chronic aphasia, an evaluation of the efficacy of intensive integrative, systematic therapy with respect to everyday communication ability is urgently needed.

### Objective

This prospective randomized controlled endpoint-blinded trial aims to examine whether, in chronic aphasia, the integrative approach to intensive language and communication therapy translates into functional improvements of everyday communication as well as improved health-related quality of life.

The principal research question is two-fold: (i) how effective is intensive integrative (i.e. combined language-systematic and communicative-pragmatic) language therapy, as currently administered in German in- and outpatient aphasia rehabilitation facilities, in improving everyday communication in post-acute/chronic post-stroke aphasia; and (ii) to what degree are these improvements maintained over a period of 6 months?

## Methods/Design^a^

The current trial uses a prospective randomized open blinded end-point (PROBE) design [26] with a waiting-list control group. The trial was approved by the Ethics Committee of the Charité – Universitaetsmedizin Berlin, Germany (No. EA1/234/11, approval received in December 2011). In addition, the study has the approval of the local ethics committees of the respective German federal states in which the 17 participating neurorehabilitation centers are located (Table 1).

**Table 1 T1:** List of participating institutions and contact person (i.e., Centre coordinator)

**Participating centre (location in italics)**	**Centre coordinator**
Max-Planck-Institut für Kognitions- und Neurowissenschaften *Leipzig* und Tagesklinik für Kognitive Neurologie ([name], [name], [name])	[name]
Brandenburg Klinik *Bernau* Waldfrieden ([name], [name])	[name]
Neurologische Klinik, Lehr- und Forschungsgebiet Neurolinguistik, Universitätsklinikum *Aachen* ([name], [name])	[name]
Städtisches Klinikum München *Bogenhausen*, Klinik für Neuropsychologie ([name], [name], [name])	[name]
Aphasiestation der Neurologischen Klinik *Bad Aibling* am Standort Rosenheim ( [name], [name], [name])	[name]
St. Mauritius Therapieklinik *Meerbusch* ([name], [name])	[name]
Median-Klinik *Grünheide*, Berlin ([name], [name], [name])	[name]
m&i Fachklinik *Enzensberg* ([name], [name], [name])	[name]
m&i Fachklinik *Bad Liebenstein* ([name], [name])	[name]
Aphasiezentrum Josef Bergmann, *Vechta* ([name], [name], [name])	[name]
Logopädisches und interdisziplinäres Behandlungszentrum für Intensivtherapie *Lindlar* ([name], [name], [name])	[name]
Asklepios Neurologische Klinik *Falkenstein* ([name], [name])	[name]
Wicker-Klinik *Bad Homburg* v.d.H. ([name], [name])	[name]
Akademische Praxis für Sprachtherapie/Neurologische Praxis *Aschaffenburg* ([name], [name])	[name]
m&i Fachklinik *Herzogenaurach* ([name], [name])	[name]
Gräfliche Kliniken Moritz Klinik *Bad Klosterlausnitz* ([name], [name])	[name]
MediClin Klinikum *Soltau* ([name], [name])	[name]

